### Withdrawal from the study and replacement

Participants can leave the study at any time for any reason if they wish to do so without any consequences. The investigator can decide to withdraw a subject from the study for urgent medical reasons, such as (but not limited to) (a) occurrence of any AE or abnormality in a laboratory assessment which warrants the subject’s discontinuation from the trial, (b) patient noncompliance defined as refusal or inability to adhere to the trial schedule or procedures, (c) at the request of a regulatory authority, (d) the patient becomes pregnant, and (e) or the patients is lost to follow-up. If so, the patient will be followed and data will be recorded in an observational manner. All data generated up to the time of discontinuation from the study will be used for the intention to treat analysis and the reason(s) for discontinuation will be recorded.

Patients who participate in the study, but drop out for the study in the first 4 weeks will be replaced by new patients. If the participant is being withdrawn because of an AE, that AE must be indicated as the reason for withdrawal. Participants who withdraw from the study will be seen for a follow-up 4 weeks later. AEs and concomitant medication will be assessed and blood will be drawn.

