#### Intervention group: mycophenolate mofetil (MMF)

Patients in the intervention group will receive oral MMF in a total daily dose of up to 2000 mg, split-dose, in addition to a prednisolone schedule, based on the EASL guidelines [27]. MMF will be started in a dosage of 500 mg, twice daily combined with prednisolone. If there are no problems with tolerability of MMF, patients will be titrated after 2 weeks to 1000 mg twice daily for the rest of the study. In case of MMF-related AEs (e.g. cytopenia), dose reduction can be considered by the treating physician. The dosage will be reduced with 250 mg twice daily until AEs disappear. When AEs persist after dose reduction, MMF can be discontinued. Those patients will be followed-up after discontinuation and will be treated according to standard of care by the treating physician. The teratogenic effect of MMF will be discussed in detail in women of childbearing potential and men who wish to father a child at the screening visit. All female patients of childbearing potential will need to undergo a pregnancy test at screening and will be instructed to take adequate anticontraceptive measures during the study.

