#### Control group: azathioprine

The control arm will receive standard of care treatment for AIH according to the recent EASL guidelines [27]. The prednisolone dosage is based on these guidelines and is identical to the intervention group. In addition to prednisolone, standard therapy consists of azathioprine in a dosage of 50 mg daily for the first 2 weeks, and 100 mg daily for the rest of the study. The patients in this group will undergo the same study schedule as the patients in the intervention group. In case of azathioprine intolerance and/or AEs, a dosage reduction is allowed from 100 mg to 50 mg daily. If AEs related to azathioprine persist at a dosage of 50 mg, discontinuation of the drug can be considered. In that case, a patient is will be withdrawn from the study and followed up by standard of care.

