### Analysis

#### Statistical analysis

Descriptive analysis will be performed for all baseline and demographic data. Normally distributed variables will be noted as mean with standard deviation (S.D.), and not-normally distributed variables will be noted as median with range or inter-quartile range (IQR) if stated. Categorical data will be noted as numbers and percentages of the total.

All randomised patients are evaluated for primary and secondary endpoints at 24 weeks. The primary analysis is based on intention-to-treat (ITT) principles. ITT analyses will be used for all clinical outcome variables. Every patient who has received at least one dose of study medication will be included in the ITT analysis. A per-protocol analysis will also be performed in patients who received >80% of the study medication. When deemed necessary, missing data will be dealt with accordingly with supportive statistical analyses (e.g. imputation or appropriate models) to assess the potential effects. These methods will be addressed in the final manuscript. Treatment effects will be analysed by comparing the difference in proportion with biochemical remission at 24 weeks between both groups. Values will be compared using Student’s *t* test, Mann-Whitney *U* test, Pearson test, Wilcoxon’s rank sum test, Wilcoxon signed-rank test, chi-square test or Fischer’s exact test, as appropriate. Time to remission will be tested and compared using a Kaplan-Meier survival analysis with log-rank test. Time to remission will be censored at 24 weeks. Significance of statistical differences is attributed to p <0.05. All statistical analyses will be performed with Statistical Package for Social Sciences (SPSS), version 22.0.

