#### Composition of the coordinating centre and coordinating

Leiden University Medical Center and Radboud University Medical Center are coordinating centres, where the principle investigators are employed. The coordinating investigators are located in both centres and have weekly digital meetings to discuss the study progress. They are responsible for the day-to-day support and are the first point of contact for gastroenterologists and hepatologists in the Netherlands. Additionally, the coordinating investigators will be responsible for the data analysis when follow-up is completed for all participants. The principal investigators are updated weekly by the coordinating investigators and are invited to meetings at least twice a year. The Dutch Autoimmune Hepatitis Working Group (DAIHWG) is updated twice yearly on the study’s progress during meetings. The DAIHWG consists of hepatologists with an interest for AIH from various (study) sites.

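### The rules for patients who stop the study drug differ by arm and conflict with each other, so the week-24 outcome of azathioprine stoppers may go missing or unused

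*Protocol article*

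**What the plan says.** Four sections of the protocol article bear on this point.

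- **Control group: azathioprine.** If adverse events persist at the reduced dose and the drug is stopped: "In that case, a patient is will be withdrawn from the study and followed up by standard of care".
- **Intervention group: MMF.** If adverse events persist after dose reduction and the drug is stopped: "Those patients will be followed-up after discontinuation and will be treated according to standard of care by the treating physician". Withdrawal from the study is not mentioned.
- **Withdrawal from the study and replacement.** For patients whom the investigator withdraws, in either arm: "If so, the patient will be followed and data will be recorded in an observational manner". The next sentence reads: "All data generated up to the time of discontinuation from the study will be used for the intention to treat analysis". The section then sets one contact with a blood draw: "Participants who withdraw from the study will be seen for a follow-up 4 weeks later". It names no week-24 visit for these patients.
- **Statistical analysis.** "All randomised patients are evaluated for primary and secondary endpoints at 24 weeks". Missing data are to be handled if that is judged necessary, and of the methods it says: "These methods will be addressed in the final manuscript".

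The primary outcome is normal ALT and IgG at 24 weeks.

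**The concern.** The same event, stopping the assigned drug for intolerance, takes a control patient out of the study and leaves an intervention patient in follow-up. If sites act on the arm-specific wording, an MMF stopper has a week-24 ALT and IgG, while an azathioprine stopper may have none, or may have one that is recorded but not used in the primary analysis.

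Azathioprine intolerance is part of the trial's rationale, so these would not be random losses. They would be tied to tolerability and, through the wording, to the arm. With 35 patients per arm, a few undetermined outcomes can shift the estimated difference in either direction, and for some results can decide significance.

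**Working it through.** **1. The wording, side by side.**

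| Question | Azathioprine stopper | MMF stopper |
|---|---|---|
| Leaves the study on stopping the drug? | Yes (control-group section) | Not stated; followed up (intervention section) |
| Week-24 visit assured? | No: standard-of-care follow-up, one visit 4 weeks after withdrawal. Yes, if the analysis section governs | Implied by continued follow-up and by the analysis section |
| Later data used for ITT? | Unclear: only data up to study discontinuation are expressly assigned to ITT; later observational data are recorded but given no role | Question does not arise unless the patient is also withdrawn |

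Azathioprine is given from week 5. A patient withdrawn before week 20 has the 4-week visit before week 24 (20 + 4 = 24), so that visit does not supply the primary outcome.

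**2. The plan's own figure.** Inputs from the sample-size section: 75.0% v 38.8%, two-sided 0.05, power 0.80, 32 per group, 35 after 10% fallout. The exact power of the two-sided Fisher test at 32 per group is 0.801, so the 32 reproduces. 32 × 1.1 = 35.2 gives the 35 (32/0.9 = 35.6).

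**3. How many outcomes are at stake.** The only stopping figure is about 15% in the first year (Background). 0.15 × 35 = 5.25, so 5 serves as an upper figure. At a constant rate over weeks 5 to 24 (20 weeks, an assumption), 5.25 × 20/52 = 2.0. Early intolerance would raise this. The range used is 2 to 5. No MMF stopping rate is given, and no MMF loss is assumed.

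**4. Effect on the test** (two-sided Fisher exact, MMF 24/35 = 68.6%, 14 azathioprine remissions observed):

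| Azathioprine outcomes missing | Left out | Counted as non-remission | Counted as remission |
|---|---|---|---|
| 2 | 14/33, p = 0.0499 | 14/35, p = 0.030 | 16/35, p = 0.090 |
| 3 | 14/32, p = 0.051 | 14/35, p = 0.030 | 17/35, p = 0.145 |
| 5 | 14/30, p = 0.084 | 14/35, p = 0.030 | 19/35, p = 0.33 |

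Near the planned rates (MMF 26/35 = 74.3%, azathioprine 12/30 = 40.0%, 5 missing), p = 0.006 (left out), 0.0016 (12/35, non-remission) and 0.049 (17/35, remission).

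**5. Effect on the estimate.** Let the azathioprine remission rate over all patients be 38.8%, MMF 75%, and 15% of azathioprine outcomes be missing. The true difference is 36.2 points.

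- Left out, no stopper in remission: 38.8/0.85 = 45.6%; difference 75 − 45.6 = 29.4.
- Counted as non-remission, 38.8% of stoppers truly in remission: 38.8 − 0.15 × 38.8 = 33.0%; difference 42.0.
- Counted as non-remission, 75% of stoppers truly in remission: 38.8 − 0.15 × 75 = 27.55%; difference 47.45.

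With 5 of 35 missing, the azathioprine rate is undetermined by 5/35 = 14.3 points.

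**The case against.** The strongest reply is that the article nowhere says the outcome is lost. Its analysis section has every randomised patient evaluated at 24 weeks. Patients withdrawn by the investigator are followed observationally in either arm. The two arm-specific sentences both end in standard-of-care follow-up, and the article expects regular visits outside the study. This stands as far as it goes: loss is a risk, not a stated consequence. It does not remove the conflict, because the article does not say which section governs or how a withdrawn patient gets a week-24 value into the analysis.

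Three stronger readings are tempting, and the article does not support them.

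- *ITT uses data only up to discontinuation.* The article says those data will be used. It does not exclude later observational data, and it speaks of leaving the study, not of stopping a drug.
- *The outcome is lost mainly in the azathioprine arm.* An adverse event can lead to withdrawal in either arm under the general withdrawal section, and no MMF stopping rate is given. The bar on additional immunosuppression within the study also leaves it unclear how an MMF stopper on other treatment would be counted.
- *The missing-data method will be picked after the results are seen, by unblinded analysts.* The sentence says where the methods will be reported. A statistical analysis plan that is not shown may fix them earlier. The coordinating investigators do analyse the data ("the coordinating investigators will be responsible for the data analysis when follow-up is completed for all participants"), but outcome assessors are to be blinded during the analyses, the analysts receive anonymised data, and ALT and IgG are laboratory values.

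It is also fair to say that the p-values crossing 0.05 come from an effect below plan and that 15% is a one-year figure. With 2 missing, 12 observed azathioprine remissions and MMF 24/35, all three handlings are significant (12/33, p = 0.014; 12/35, p = 0.008; 14/35, p = 0.030).

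**Conclusion.** The concern holds as a contradiction between sections with a difference between the arms. As written, the rules can lead to different ascertainment of the week-24 primary outcome by arm, and the losses would be related to tolerability. An analysis plan could settle how missing values are handled, but it would not reconcile the two arm-specific rules or recover bloods that were never collected.

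The size is conditional. With 2 to 5 of 35 azathioprine outcomes missing, none missing on MMF, and an observed effect somewhat below plan, the handling decides significance. Near the planned rates it does not, though the estimate still moves. Counting all missing patients as in remission is an extreme bound, not an expectation.

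**What to change.** Reconcile the withdrawal, MMF, azathioprine and statistical analysis sections so that stopping the assigned drug is separated from leaving the study in the same way in both arms. This concerns data collection only; clinical care stays as it is.

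Retrieve week-24 ALT and IgG for every randomised patient, whatever their treatment status, and state that these values enter the ITT analysis. Routine bloods suffice. Retrieval comes first, because a missing-data rule that is identical on paper still acts unequally if values are missing in one arm only.

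Before database lock, fix one rule for both arms for any week-24 value still missing, for example counting it as not in remission, and give the alternative as a sensitivity analysis.

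The cost is a wording change, some data retrieval for a handful of patients, and possibly slightly lower observed remission rates. The article reports 66 of 70 patients randomised with the trial still running, so at that point the change was still possible.

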#### Concomitant care

Concomitant medication may be given as medically indicated. No additional immunosuppression is allowed within the study. Participants are not allowed to participate in other (experimental) trials investigating pharmaceutical agents or strategies aimed at AIH.

#### Drug accountability

Study medication will be stored and distributed to patients according to GCP regulation and national law. Drug accountability will be performed by the (local) investigator using a drug accountability log. At the trial beginning, participants will be asked to take their medication to the clinic to control compliance. Follow-up is at least once a month to actively remind patients.

### Outcomes

#### Primary outcome

The primary outcome is the percentage of patients in biochemical remission, defined as normalisation of serum ALT and IgG levels, per treatment group. This primary endpoint will be assessed at 24 weeks of treatment.

#### Secondary outcomes

The secondary outcomes are to evaluate the efficacy of MMF versus azathioprine in combination with a 24-week prednisolone taper regimen in patients with AIH measured by the following:Biochemical remission at 24 weeks and at anytimeTime to biochemical remissionComplete biochemical response: defined as normalisation of AST, ALT, and IgG at 24 weeksNon-response at 4 weeks: defined as <50% decrease of serum transaminases within 4 weeks after initiation of treatmentInsufficient response: defined as lack of complete biochemical response determined at 24 weeksChanges in MELD score (and its components bilirubin, INR, creatinine), and in albuminChanges in liver stiffness, measured by transient elastographyN-terminal procollagen-III-peptide, Enhanced Liver Fibrosis (ELF) scoreChanges in quality of life measured with Short Form (SF)-36Difference in side-effects, AEs and serious AEs (SAE), based on clinical examination (e.g. hypertension), laboratory assessments (e.g. neutropenia and new-onset diabetes), and patients-reported symptoms between the MMF and azathioprine groupsThe level of ALT, AST, gamma-glutamyl transferase (GGT) in both groupsPercentage of patients with biochemical remissionRatio of ALT to lowest ALT everExtrahepatic AIH manifestations (e.g. arthralgia)Patient survivalFatigue indexPruritis visual analogue scoreDifference in cumulative corticosteroid dose between the MMF and azathioprine groups

Ancillary studies can be performed on blood samples as determined by the Dutch AIH Group steering committee.

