### Study design and recruitment

CAMARO is a phase IV, randomised (1:1), open-label, parallel-group, multicentre superiority trial in 70 patients with treatment-naive AIH. All patients with established AIH according to the simplified criteria for the diagnosis of AIH [32] and who are considered for induction therapy will be eligible for the study. Eligibility will be assessed at the screening visit (SV) and patients will start with prednisolone according to the treatment schedules in Tables 2 and 3. A patient may enter the study at any time point in the first 4 weeks, as long as the prednisone schedule has been used for induction therapy. After informed consent, patients will be randomised in a 1:1 ratio to one of the two treatment arms. At 4 weeks, patients will consequently start with either azathioprine or MMF in dosages exactly according to the schedule (Tables 2 and 3). Eight follow-up visits are scheduled at weeks 4, 8, 12, 16, 20, and 24. The week 24 visit is the end of the treatment visit. After that, patients can continue azathioprine or MMF as assigned, as maintenance therapy. A trial flowchart is shown in Fig. 1.

**Table 2 Tab2:** Treatment schedule for patients 40–80 kg

Week	Prednisolone (mg/day)	Azathioprine (mg/day)	MMF (mg/day)
1	40	-	-
2	30	-	-
3	25	-	-
4	20	-	-
5	15	50	1000
6	12,5	50	1000
7[contact]
9+10	7,5	100	2000
From week 11 onwards	5	100	2000

*MMF* mycophenolate mofetil, *mg* milligrams

**Table 3 Tab3:** Treatment schedule for patients >80 kg

Week	Prednisolone (mg/day)	Azathioprine (mg/day)	MMF (mg/day)
1	60	-	-
2	45	-	-
3	30	-	-
4	20	-	-
5	15	50	1000
6	12,5	50	1000
7[contact]
9+10	7,5	100	2000
From week 11 onwards	5	100	2000

*MMF* mycophenolate mofetil, *mg* milligrams

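### Week-4 non-response is listed as an efficacy outcome for MMF versus azathioprine, but neither drug has been given by week 4

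*Protocol article*

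**What the plan says.** The list in the Secondary outcomes section opens by giving its purpose: "The secondary outcomes are to evaluate the efficacy of MMF versus azathioprine in combination with a 24-week prednisolone taper regimen". One item is non-response at week 4, "defined as <50% decrease of serum transaminases within 4 weeks", counted from the start of treatment.

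The Study design and recruitment section sets the order of treatment. Prednisolone comes first: "Eligibility will be assessed at the screening visit (SV) and patients will start with prednisolone according to the treatment schedules". The randomised drugs follow: "At 4 weeks, patients will consequently start with either azathioprine or MMF in dosages exactly according to the schedule". Tables 2 and 3 agree. Both drug columns hold dashes for weeks 1 to 4, and the first doses stand in week 5. The two tables differ by body weight, not by arm, and the control-group section confirms that the steroid does not differ between arms: "The prednisolone dosage is based on these guidelines and is identical to the intervention group".

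The same secondary list includes remission at any time and time to remission. For the latter, the Statistical analysis section gives an end point, "Time to remission will be censored at 24 weeks", but no explicit starting point.

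**The concern.** An outcome can inform a comparison of two drugs only if it is measured after at least one of them has been taken. Here the assessment closes the prednisolone run-in, before either drug starts. The stated purpose of the list and the timing of this item contradict each other.

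At stake is a secondary result that could be read as early evidence for or against MMF. A nominally significant difference at week 4 would look like efficacy and could not be. A null result would look like early equivalence and would be equally uninformative. Patients who already meet the remission definition at the week-4 visit raise a related, weaker question for remission at any time and time to remission: they count as events although they have taken no randomised drug.

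**Working it through.** The article gives no figure for the week-4 outcome, so there is none to reproduce. Its sample size concerns the week-24 endpoint and is used here only for the number per arm.

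**Inputs**
- Start of MMF or azathioprine: week 4, first doses in week 5 (Study design and recruitment; Tables 2 and 3).
- Assessment: week 4, counted from the start of treatment (Secondary outcomes).
- Patients per arm: 35 (Sample size calculation).
- Threshold p<0.05, with chi-square or Fisher's exact test among the listed options (Statistical analysis).
- True week-4 non-response rate: not given; assumed 10% to 50%, equal in both arms.

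**Step 1: exposure at the assessment**

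Exposure = assessment week − start week = 4 − 4 = 0 weeks, in both arms. Up to then the arms share one prednisolone schedule, so the expected drug effect is zero.

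**Step 2: which start of treatment is meant**

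If treatment began with the first MMF or azathioprine dose, the assessment would fall at week 4 + 4 = 8. The article's clock points the other way. Tables 2 and 3 number the weeks from the first prednisolone dose, the outcome is labelled as a four-week one, visits are numbered 4 to 24, and "The week 24 visit is the end of the treatment visit". On that clock, week 4 is the visit at which the randomised drug begins.

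**Step 3: what a test at week 4 would return**

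With a common true rate p and n = 35 per arm, the chance of p<0.05 is the sum, over all pairs (i, j) for which the test rejects, of Bin(i; 35, p) × Bin(j; 35, p). The standard error of the observed difference is √(2p(1−p)/35). At p = 0.1 this is √(0.18/35) = 0.072; at p = 0.5 it is √(0.50/35) = 0.120.

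| Assumed rate in both arms | Chi-square p<0.05 | Fisher p<0.05 | SE of difference |
|---|---|---|---|
| 10% | 5.7% | 1.3% | 7.2 points |
| 20% | 4.9% | 2.5% | 9.6 points |
| 30% | 5.1% | 2.8% | 11.0 points |
| 40% | 4.8% | 2.8% | 11.7 points |
| 50% | 4.3% | 2.4% | 12.0 points |

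These are false-positive rates, and any apparent power for a drug effect equals them. They assume no selection or adherence difference between arms.

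**Step 4: remission at any time and time to remission**

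Let r be the share in remission at the week-4 visit, equal in both arms, with all of them counted as events. The between-arm difference in remission at any time is then (1 − r) times the difference among the remaining patients. The article gives no r. If r = 0 there is no dilution. The log-rank statistic would then also be the same with a clock starting at week 0 or at week 4, because it depends on the order of events and not on elapsed weeks.

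**The case against.** The best defence has four parts.

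- **The definition is ambiguous.** It counts from the start of treatment, which could mean the randomised drug. The label and week numbering make this the weaker reading, and if it was intended, the label is wrong. The text needs correcting either way.
- **The list is mixed.** Under the same lead-in stand adverse events, survival and cumulative steroid dose, and no specific test is named for this item. That is fair: the article does not show that a stand-alone efficacy claim is planned. It does place the item under that purpose without separating it.
- **Counting from the start of treatment is legitimate for remission.** The Discussion cites a standardised endpoint timed that way. This stands, and the time origin should not be moved to week 4.
- **The change comes late.** Under Trial status, 66 of 70 patients are randomised, and amendments go to the ethics committee. This argues for a small change.

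A reader might also infer several stronger points that the article does not support:

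- *A week-4 difference can only be chance, with a 5% false-positive rate.* Patients may be randomised at any time in the first 4 weeks, allocation is open, and those who drop out in that period are replaced. Selection or adherence could therefore also produce a difference. The rate depends on the test and is lower with Fisher's.
- *4 of 24 weeks, or 17% of the information, carries no contrast.* That is a share of calendar time, not of log-rank information.
- *A prognostic covariate is lost.* Reporting a variable as an outcome does not prevent its use as a covariate.
- *Week-4 response belongs in the baseline table.* For patients randomised before week 4 it is a post-randomisation value.

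**Conclusion.** The point holds for week-4 non-response. As written, the outcome cannot serve the purpose the list assigns to it, because exposure to MMF and azathioprine at that assessment is zero weeks in both arms. A difference there could reflect chance, selection or adherence, but not an effect of one drug against the other. This rests on the article's own week numbering, with treatment starting at the first prednisolone dose. The false-positive rates rest on 35 per arm and on assumed non-response rates of 10% to 50%.

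For remission at any time and time to remission, only a limited point holds. Patients in remission at week 4 would count as events before any randomised drug, and the size of any dilution cannot be derived from the article.

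The consequence is confined to secondary outcomes. The week-24 primary endpoint and its sample size are untouched.

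**What to change.** 1. Report week-4 non-response as a descriptive measure of response to prednisolone, overall and by arm, with no efficacy test.
2. If a drug comparison was intended, state instead that treatment starts with the first MMF or azathioprine dose, and correct the four-week label and the visit (week 8 on the study clock). State the reference value for the percentage decrease as well. Week-4 transaminases are already lowered by prednisolone, so a 50% threshold applied to them would mean something different.
3. For remission at any time and time to remission, keep the time origin and write it down. Report the number per arm already in remission at the week-4 visit, and add a sensitivity analysis excluding them. Read that analysis with the open-label caveat, since week 4 can follow randomisation.

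No new data are needed: under Other outcomes, ALT, AST and IgG are already drawn at weeks 0, 4 and 8. The cost is a minor late change to one secondary outcome plus one added sensitivity analysis. It should be documented before the final analysis, with an amendment if the outcome is redefined.
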